### Sample size calculations

Based on previous reports on the topic [10], we estimated that a total sample of at least 340 older adults with acute infections would be sufficient to detect a minimal clinically significant difference in Frailty Index (FI) of at least 0.03 points from the pre-admission status to hospital discharge, with an alpha of 0.05, and a power of 80%.

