### Statistical analysis

The baseline characteristics of the study participants will be described using count and proportion for the categorical variables and mean and standard deviation, or median and interquartile ranges, for the quantitative variables, according to their distribution. These characteristics will be compared between participants by type of infection and the presence of systemic inflammatory response through the ANOVA, Student t-test, Kruskal Wallis test, or Chi-squared test, as appropriate.

The intra-individual change in FI between the pre-admission status and the patient’s condition at hospital discharge will be evaluated through the Student t-test for paired samples and then with linear mixed models. The latter analysis will be set with a random intercept and slope and adjusted for potential confounders in the association between infectious diseases and frailty changes, e.g., sociodemographic information, study center, comorbidities, length of hospital stay, and in-hospital clinical events (unrelated to the infection). The mean adjusted change in FI between pre-admission status and hospital discharge will be expressed as ß coefficient and 95% confidence interval (95% CI). Moreover, we will test whether the presence of systemic inflammation will modify the average intra-hospital change in FI. As secondary analyses, we will investigate which infection-related characteristics will be associated with higher in-hospital mortality (through the Kaplan-Mayer method and Cox regression analysis), longer hospital stay (with linear regressions), and discharge setting (with multinomial logistic regression).

The impact of infectious diseases (distinguished by number, site and severity) on frailty changes will be analyzed with linear mixed models, considering the beta coefficients (95% CI) for the interaction infection*time. Additional analyses will be performed to test whether sociodemographic, functional, clinical, and genetic/epigenetic factors interact with infectious diseases to influence the course of frailty over time.

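### Linear regression of hospital stay treats a stay ended by death as a short stay; a model of time to live discharge with death as a competing event suits the question better

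*Protocol article*

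**What the plan says.** The Statistical analysis section of the Protocol article introduces three secondary outcomes together: "As secondary analyses, we will investigate which infection-related characteristics will be associated with higher in-hospital mortality", followed by length of stay and discharge setting. Mortality is given Kaplan-Meier and Cox methods, discharge setting is given multinomial logistic regression, and stay is given as "longer hospital stay (with linear regressions".

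The article states no scale for stay (days or log days) and does not say how a stay that ends in death enters the regression. The same section does take account of distribution, but only for the descriptive summaries: "mean and standard deviation, or median and interquartile ranges, for the quantitative variables, according to their distribution".

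The design is sized for the Frailty Index alone. The Sample size calculations section says that "a total sample of at least 340 older adults with acute infections would be sufficient" for a "difference in Frailty Index (FI) of at least 0.03 points from the pre-admission status to hospital discharge". No mean, spread, effect size or group split is given for length of stay, and no expected mortality.

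**The concern.** Two features of length of stay fit badly with ordinary linear regression.

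- **Death as a competing event.** The plan studies the same infection characteristics against in-hospital death and against stay. If a severe infection both slows recovery and kills some patients early, the early deaths enter the stay regression as short stays and offset the longer stays of the survivors. Leaving the deaths out instead restricts the comparison to survivors, who are selected differently in the severe and mild groups. Linear regression has no place for the competing event either way.
- **Right skew.** Stay is positive and usually has a long upper tail. On raw days a few very long stays can dominate the estimate.

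At stake is one of the adverse endpoints that the Discussion puts forward as a main contribution of the project. A characteristic that truly delays discharge could look unimportant.

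**Working it through.** **1. The plan's own figure.** There is none for stay. The only design figure is 340, "with an alpha of 0.05, and a power of 80"%, for a 0.03 change in Frailty Index. No SD is given, so it can only be inverted. As a paired comparison, SD of change = 0.03 × √340 / (1.960 + 0.842) = 0.197. This says nothing about stay.

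**2. Effect of death on the regression of days.** Let m be mean stay in patients discharged alive, d mean days to death, and p in-hospital mortality. Subscript 1 is the severe group and 0 the other. Mean recorded stay is (1 − p)m + pd, so the regression estimates

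(1 − p₁)m₁ + p₁d − (1 − p₀)m₀ − p₀d.

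All inputs are assumptions: m₀ = 10, m₁ = 13 (a 3-day prolongation among those discharged alive), p₀ = 5%. For d = 5 and p₁ = 20%: 0.80 × 13 + 0.20 × 5 = 11.40; 0.95 × 10 + 0.05 × 5 = 9.75; difference 1.65 days.

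| Mean days to death | p₁ = 10% | p₁ = 20% | p₁ = 30% |
|---|---|---|---|
| 3 | 2.35 | 1.35 | 0.35 |
| 5 | 2.45 | 1.65 | 0.85 |
| 8 | 2.60 | 2.10 | 1.60 |

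With equal mortality of 5% in both groups the difference is 0.95 × 3 = 2.85 days, so the shrinkage comes mainly from unequal mortality. If deaths come late the direction changes: with d = 15 and p₁ = 20%, 13.40 − 10.25 = 3.15 days.

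**3. Logging does not cure this.** Take 10, 13 and 5 as geometric means, a true ratio of 1.30. With p₁ = 20%, the mean log stay is 0.80 × ln 13 + 0.20 × ln 5 = 2.374, against 0.95 × ln 10 + 0.05 × ln 5 = 2.268. The difference of 0.106 is a ratio of 1.11. With p₁ = 30% the severe group's mean is 2.278 and the ratio is 1.01.

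**4. Raw against log scale, ignoring death.** Simulated power, 170 v 170, two-sided 0.05. The even split, the distribution and the effect are all assumed.

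| Assumed stay | Effect | Raw days | Log days | Log minus raw |
|---|---|---|---|---|
| Log-normal, log-SD 0.6 / 0.7 / 0.8 | 20% longer | 72.0 / 56.0 / 43.2% | 79.2 / 66.5 / 54.8% | +7.2 / +10.5 / +11.6 |
| Log-normal, log-SD 0.6 / 0.7 / 0.8 | 25% longer | 87.7 / 73.7 / 59.0% | 92.6 / 83.7 / 72.5% | +4.9 / +10.0 / +13.5 |
| Gamma, CV 0.5 / 0.7 / 0.9 | 20% longer | 91 / 67 / 45% | 88 / 56 / 33% | −3 / −11 / −12 |

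Over log-SD 0.4 to 1.0 and uneven splits, with the effect set to give the log model 80% power, the log-normal loss ran from 1.8 to 24.1 points. A gamma model with log link gave 72 / 56 / 44% in the first row's setting, essentially the same as raw days. Type I error on raw days stayed between 4.5% and 5.5% in every log-normal setting.

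**5. Influence of long stays.** Under log-normal stay with log-SD 0.5 to 0.8, the 5 longest of 340 stays carry on average 25% to 39% of the total sum of squares on raw days.

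**The case against.** The strongest reply is that a journal article naming a model family has fixed very little. A linear regression of log days is still a linear regression, and transformation, residual checks and influential points are usually left to the analysis plan. This stands: a reader might infer that the trial will analyse raw days, but the article does not say so.

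A reader might also infer that the trial gives up a known amount of power by not logging. The documents give nothing from which to compute that, and step 4 shows that the sign depends on the distribution. Log-normal is the case in which the log model is optimal by construction. The two models also answer different questions: a difference in mean days, which bears on bed use, and a ratio of geometric means. Nor is the raw-scale test invalid at this sample size.

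It can further be said that terminally ill and more severely frail patients are excluded (Study design and participants), so deaths may be few. That limits the size of the problem. It does not remove it, because the plan itself sets out to analyse in-hospital mortality by the same characteristics.

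What the reply does not reach is the competing event. It affects linear regression on either scale, so stating a transformation would not resolve it.

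**Conclusion.** The point holds as a cheap improvement. The named method for length of stay does not separate slow recovery from early death, although the same sentence of the plan shows that deaths are expected. The estimated prolongation can be understated or hidden. In the assumed scenarios with earlier deaths and 10% to 30% mortality in the severe group, a 3-day prolongation appears as 0.35 to 2.60 days. These figures rest on assumed stays, times to death and mortality, and the bias is small if mortality is low or similar across groups.

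The influence of a few long stays is a real but secondary matter, and applies if days are analysed untransformed. The contrast of about 5 to 14 points of power should be quoted only as conditional on log-normal stay with log-SD 0.6 to 0.8, an even split and a 20% to 25% effect; it reverses under gamma stay. It supports no claim that the log scale is better for this trial.

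The analysis is secondary. The primary Frailty Index analysis and the sample size of 340 are unaffected.

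**What to change.** Replace the linear regression for length of stay by a model for time from admission to live discharge, with in-hospital death as a competing event. Report cause-specific or subdistribution hazard ratios with 95% CI, and say which. A hazard ratio below 1 then means slower live discharge. A subdistribution ratio also reflects deaths, so it should be read beside the mortality analysis that the plan already contains.

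Keep linear regression of days as a descriptive supplement, with its scale stated, the handling of deaths stated, and influential long stays checked.

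The cost is analysis wording only: length of stay and discharge setting are already outcomes of the plan, and in-hospital death is already analysed over time. The downside is that hazard ratios are less intuitive than extra days; median or predicted stay by group can be added.

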## Discussion

This project will investigate the relationship between infections in hospitalized older patients and frailty trajectories over time. Frailty is a cornerstone of geriatric clinical practice because it is associated with adverse health outcomes, including hospitalization, length of hospital stay, falls, delirium, and mortality [2, 30]. The INFRAGEN project will provide novel contributions to this area of research in four main ways.

First, the study will quantify the impact of infections on the change in individuals’ frailty status from pre-admission to hospital discharge. Evidence from the SARS-CoV-2 pandemic suggests that infectious diseases can substantially promote frailty development even beyond 3 months of acute illness [7, 8]. However, data on how the most common types of infection, their severity, the occurrence of multiple infectious diseases, and their related level of systemic inflammation may influence the progression of frailty in older adults are lacking. Furthermore, there is some heterogeneity in the definitions of frailty adopted across various studies. Second, the project will explore the interaction between infections and in-hospital frailty status in influencing adverse endpoints, such as in-hospital mortality, length of hospital stay, and discharge destination. For instance, sepsis in frail patients has been shown to worsen mortality compared to non-frail patients [31], and other infections such as pneumonia, COVID-19, or influenza may have similar detrimental impacts [32–34]. Additionally, frailty is linked to a higher risk of urinary tract infections [35]. Third, the project will assess whether global DNA methylation and telomere length patterns at hospital admission are predictors of in-hospital and post-discharge frailty trajectories. In the literature, these epigenomic and genomic markers have been linked to cellular senescence and aging [36]. For example, shorter LTL have been associated with increased risk of infections, various malignant tumors (esophageal cancer, lymphoid and myeloid leukemia), and mortality from cardiovascular, respiratory, digestive, and musculoskeletal diseases and COVID-19 [11]. However, the role of these genomic markers in predicting frailty or functional changes has not been fully investigated [13]. This project will allow us to explore whether DNA methylation and telomere length variations are involved in the pathogenetic processes leading to frailty, especially following an infection. Notably, epigenetic modifications and telomere attrition (dynamic epigenomics) are sensitive to exogenous and endogenous stressors, which strongly relates to an individual’s baseline epigenome and their personal response to stressors, thus accounting for the relationship between epigenomic patterning and developmental trajectories or disease [37]. Although a 3-month period may be a short time interval to detect changes in LTL, we cannot rule a negative impact of infectious diseases and inflammatory processes on this aspect in vulnerable individuals, such as older inpatients. Moreover, blood cells composition of the included participants is expected to change between in-hospital and post-discharge assessments, and this issue may further influence LTL.

Finally, the INFRAGEN project will clarify which inflammatory markers (e.g., Interleukins 1 to 18, GDF15, IF1, TNFR, MCP-1) are mostly predictive of frailty progression and adverse health-related outcomes in older adults with acute infections. Frail individuals are known to have significantly reduced innate immune function, T-cell activity, antibody production, and a persistent state of chronic mild inflammation. However, longitudinal studies have not demonstrated a clear association between higher inflammatory levels and the onset of frailty [4]. Research in this field may help contribute to the current literature on the relationship between inflammatory markers, frailty pathophysiological pathways, and patient clinical phenotypes. By enrolling patients with no or only mild frailty before hospital admission and who are affected by acute infections generally triggering inflammation, we will be able to derive a risk stratification of frailty development based on inflammatory, genetic/epigenetic and clinical factors.

The INFRAGEN project has several strengths, including multicenter patient enrollment, standardization of biochemical and genomic analyses in a central laboratory, and broad multidomain characterization of older patients. Moreover, combining clinical and pre-clinical research expertise will allow us to provide novel findings that will contribute to the pathophysiological understanding of frailty and may have concrete implications for clinical practice. Potential critical points may include the recruitment of patients with no or mild frailty in acute geriatric units, which may be challenging because older adults needing hospitalization are often clinically complex and frail at the time of admission. However, the coordination of participating centers may transform these potential challenges into opportunities to investigate understudied topics. Another limitation of our study is the relative homogeneity of the older Italian population, which is still predominantly Caucasic and may make our results not generalizable to other ethnic groups. The generalizability of the project findings may also be affected by the involvement of only Italian Geriatric units. However, these wards exhibit some differences in terms of hospital organization, infection epidemiology, and regional healthcare practices, which partly account for the heterogeneity of healthcare systems.

Regarding dissemination activities, the project results will be published in scientific papers submitted to international biomedical journals. Additionally, study team members will participate in national and international conferences to further disseminate the project findings and their potential translational clinical implications. These efforts will highlight the importance of stimulating clinical and pre-clinical research in this field.

## Conclusions

The INFRAGEN study will contribute to understanding the role of infections and inflammation in prompting the development of frailty in older adults. Additionally, it will explore whether genetic and epigenetic factors, such as global DNA methylation and telomere attrition, may modify the impact of infections on frailty trajectories during hospitalization and after hospital discharge. Therefore, the results of this project will help clarify the underlying pathophysiological mechanisms of frailty and stratify the risk of frailty and other adverse outcomes (e.g. mortality, prolonged hospital stay, repeated hospital readmissions, infection recurrence, or reduced independence) in older inpatients with acute infections.

## Data Availability

No datasets were generated or analysed during the current study.

## Abbreviations

CFS: Clinical Frailty Scale
FI: Frailty Index
ICD-9: International Classification of Diseases, Ninth Revision
BADL: Basic Activities of Daily Living
IADL: Instrumental Activities of Daily Living
SPMSQ: Short Portable Mental Status Questionnaire
CIRS: Cumulative Illness Rating Scale
MNA-SF: Mini Nutritional Assessment Short Form
ESS: Exton-Smith Scale
GDS: Geriatric Depression Scale
SOFA: Sequential Organ Failure Assessment
LTL: Leukocyte Telomere Length
